### Secondary outcomes

Behaviour is measured using the Strengths and Difficulties Questionnaire (SDQ)^36^ at baseline, 3 and 6 months. The SDQ is a brief behavioural screening questionnaire. It contains 25 items divided between five scales: emotional symptoms; conduct problems; hyperactivity/inattention; peer relationship problems and prosocial behaviour. It takes 5–10 min to complete and is completed with the young person.ADHD symptoms are measured using the Brief Barkley ADHD Rating Scale (B-BAARS)^37^ at baseline, 3 and 6 months. The B-BAARS is a newly developed short (six item) screen for ADHD. It takes 5 min to complete and is completed with the young person.Health-related quality of life is measured using the Child Health Utility Instrument^38^ at baseline, 3 and 6 months. It takes 5 min to complete and is completed with the young person.Objective rating of symptoms and functioning is measured by the Swanson, Nolan and Pelham Questionnaire (SNAP-IV 26)^39^ and Children’s Global Assessment Scale (C-GAS)^40^ at baseline, 3 and 6 months. The SNAP-IV 26 screens for nine symptoms of ADHD hyperactive-impulsive type, nine symptoms of ADHD inattentive type and eight symptoms of oppositional defiant disorder as defined in the Diagnostic and Statistical Manual of Mental Disorders, 4th edition. The SNAP-IV is completed by a teacher within the CYPSE. The C-GAS is a 0–100 scale completed by a clinician which integrates psychological, social and academic functioning.Number and duration of (in minutes) consultations/appointments until confirmed ADHD diagnosis as recorded on a pro forma completed by clinicians after each consultation with the young person.Number of days until a confirmed diagnosis is reached using file information.Contact with services is measured using the modified Client Service Receipt Inventory^41^ at baseline, 3 and 6 months. It takes 5–10 min to complete and is completed with the young person.Number of reordered behavioural incidents and adjudications are collecting using prison file information at baseline, 3 and 6 months.

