QbTest demonstrates good psychometric properties^28 29^ and has the additional benefit over other computer tasks of measuring activity level, a core symptom of ADHD.^30^ There are several studies that demonstrate the clinical utility of QbTest in aiding diagnosis.^31 32^ A recent randomised controlled trial found clinicians with access to the QbTest report were more likely to reach a diagnostic decision about ADHD. At 6 months, 76% of those with a QbTest report had received a diagnostic decision, compared with 50% without a QbTest report. QbTest reduced appointment length, increased clinicians’ confidence in their diagnostic decisions and doubled the likelihood of excluding ADHD.^33^

The use of the QbTest in the community looks promising.^34^ However, there are a number of unknowns in relation to its use in the CYPSE. Implementing new approaches can require more planning due to the regime; therefore, the potential barriers and facilitators to implementation need to be understood. The young people within the CYPSE are more complex and have greater comorbidity than young people accessing community Child and Adolescent Mental Health Services. The acceptability of the QbTest needs to be assessed to see if the same positive findings can be replicated. Primary outcomes in previous QbTest trials^33^ have been time to diagnosis, but given the comparative short stay in the CYPSE and difficulty obtaining these data once they leave, it is unclear how reliably these data can be collected and/or if other outcomes, such as in aggressive incidents, are more important in this population.

The longer term aim is to undertake a definitive randomised controlled trial of the effectiveness of QbTest in the assessment of ADHD in the CYPSE. An evidence base within the CYPSE needs to be developed in order to change policy and implement the QbTest across the whole system. In line with the Medical Research Council (MRC) guidelines on developing complex interventions and as randomised controlled trials within the CYPSE are scarce, a feasibility study is required.^35^

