### Intervention: QbTest plus usual care

Once the young person has been referred to the multidisciplinary team, the young person is booked into the QbTest clinic. The healthcare team will conduct the QbTest and use the information from the QbTest report in conjunction with the clinical information (patient history, observation and ADHD symptom questionnaire) to inform their decision whether the young person has ADHD or not. Young people randomised to the QbTest will receive usual care, as outlined above plus the QbTest. The QbTest takes approximately 20 min to complete and the results will be discussed with the psychiatrist and the young person; this will take approximately 10 min.

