### Data analysis and management

Data analysis will be mainly descriptive.^44^ All measures will be summarised by group across follow-up time with mean and SD for normally distributed data, median for skewed variables and frequency (percentage) for categorical data. All statistical analysis will be conducted using Stata V.15. No interim analysis is planned.

Interviews will be conducted and recorded by the researcher using an encrypted Dictaphone. All qualitative data will be analysed using thematic analysis^45^ with the aid of NVivo. Data will be coded inductively into themes, creating a detailed coding scheme, allowing for the investigation of emergent patterns between individual codes and boarder emergent themes.

Data will be double entered and stored on an encrypted and password-protected database at the University of Manchester. Double-entered data will be compared for discrepancies and discrepant data will be verified using the original paper data sheets (between [name] and CL).

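### Consultations are counted only to a confirmed ADHD diagnosis, and days to an ambiguous confirmed diagnosis, although the protocol describes the benefit of QbTest as a decision either way

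*Protocol article*

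**What the plan says.** Two items under Secondary outcomes in the protocol article use a diagnosis as their endpoint. The first is the number and duration of "consultations/appointments until confirmed ADHD diagnosis as recorded on a pro forma completed by clinicians after each consultation". The second is "Number of days until a confirmed diagnosis is reached using file information". The first names ADHD; the second does not.

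Data analysis and management applies one descriptive rule to everything: "All measures will be summarised by group across follow-up time with mean and SD for normally distributed data, median for skewed variables", with frequencies and percentages for categorical data.

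The rationale is worded differently. Of the earlier community trial, the Introduction says: "At 6 months, 76% of those with a QbTest report had received a diagnostic decision, compared with 50% without a QbTest report". It adds that QbTest "doubled the likelihood of excluding ADHD". The intervention section says the report is used with the clinical information "to inform their decision whether the young person has ADHD or not". In these places the result of interest is a decision in either direction.

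Table 1 separately lists ADHD diagnosis and clinical confidence as a follow-up item. Sample size and recruitment justifies 60 participants partly as enough to give a mean and SD for each outcome measure.

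**The concern.** The consultation outcome has an endpoint only when ADHD is confirmed. If the assessment ends by ruling ADHD out, it has finished, but the outcome as worded has no stopping point. The days outcome has the same gap if its confirmed diagnosis means a positive one. That reading is plausible, because the Exclusion criteria use the phrase in that sense, but it is not certain.

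There is a second group without a value: young people still undecided when file information ends. The Introduction leads one to expect them, since it says informant information often fails to arrive before release. A plain mean or median over those with a value would leave them out. Whether someone is decided by 6 months is itself something QbTest is expected to change, so the retained subset would be selected differently in each arm.

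What is at stake is planning. The Introduction says time to diagnosis was the primary outcome of previous QbTest trials and asks whether it can be collected reliably in custody. If this trial describes it on a selected subset, the definitive trial could inherit a misleading location and SD, or reject a usable endpoint.

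**Working it through.** **The plan's own figure.** 5 per month × 12 months = 60, or 30 per arm, which agrees with the stated sample. This checks recruitment arithmetic only. No alpha, power or effect size is stated, so there is no power claim to test.

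**Inputs from the article.** 30 per arm (Trial design; Sample size and recruitment). Decided at 6 months: 76% with a QbTest report, 50% without (Introduction, community trial). 6-month point: T = 182 days (Follow-up).

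**Assumptions.** The community rates carry over to custody. Time to decision is Weibull, with shapes 0.7 to 2 tried; shape 1 is a constant hazard.

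**Step 1: who has no value.** Undecided at 6 months: 30 × (1 − 0.76) = 7.2 with QbTest and 30 × (1 − 0.50) = 15 in control.

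**Step 2: constant hazard.** Let p be the proportion decided by T.
- Hazard h = −ln(1 − p)/T: 1.427/182 = 0.00784 and 0.693/182 = 0.00381 per day.
- Restricted mean to T, all randomised = p/h: 0.76/0.00784 = 97 and 0.50/0.00381 = 131 days. Difference about 34.
- Mean among the decided = [restricted mean − T(1 − p)]/p: (96.9 − 43.7)/0.76 = 70.1 and (131.3 − 91.0)/0.50 = 80.6 days. Difference about 10.5.
- Median, all randomised = ln 2/h: 88 and 182 days, difference 94. Median among the decided: 61 and 76 days, difference about 15.

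Means should be compared with means and medians with medians. On means, 34 days becomes about 10.5; on medians, 94 becomes about 15.

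**Step 3: other shapes.** S(t) = exp[−H(t/182)^k], with H = −ln(1 − p), so each curve still passes through 76% or 50% at day 182.

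| Shape k | Restricted mean, QbTest v control | Difference | Decided-only mean, QbTest v control | Difference |
|---|---|---|---|---|
| 0.7 | 84.6 v 123.2 | 38.5 | 53.9 v 64.3 | 10.4 |
| 1.0 | 96.9 v 131.3 | 34.4 | 70.1 v 80.6 | 10.5 |
| 1.5 | 112.0 v 140.9 | 28.8 | 89.9 v 99.7 | 9.8 |
| 2.0 | 122.7 v 147.4 | 24.7 | 104.0 v 112.8 | 8.9 |

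The all-randomised difference is 25 to 39 days and the decided-only difference about 9 to 10.5. The decided-only summary keeps 27% to 36% of the difference, so it loses 64% to 73%.

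**Step 4: exclusions.** Let e be the proportion of randomised controls in whom ADHD is excluded, and read doubled as a risk ratio of 2 (the article gives neither e nor the scale). Confirmed diagnoses are then 0.76 − 2e with QbTest and 0.50 − e in control, a difference of 0.26 − e.
- e = 5%: 21 points
- e = 13%: 13 points
- e = 20%: 6 points
- e = 26%: 0 points

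Anything from nearly all to none of the 26-point difference could remain in confirmed diagnoses. Without e, the share lying in exclusions cannot be determined.

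**The case against.** There are several fair points on the plan's side.

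- **The days item may already cover both results.** It omits ADHD, and the Introduction calls the earlier primary outcome time to diagnosis while reporting a diagnostic decision. A reader might infer that both outcomes count positive diagnoses only; the text supports that clearly for consultations alone. The two items then need reconciling.
- **No rule drops anyone.** A reader might infer that excluded and undecided participants will be omitted. The article does not say so, and an analysis plan that is not shown could set a censoring rule; its absence here is no fault. This stands for the undecided. It does not answer the event definition: censoring cannot make an exclusion an endpoint while the endpoint is a confirmed ADHD diagnosis.
- **Diagnosis status is recorded anyway.** Table 1 has the item, and frequencies are planned, so a proportion by arm can be reported. This stands, but it does not repair the time and consultation outcomes.
- **The size rests on assumptions.** A reader might infer that most of the QbTest effect is hidden, or set the 94-day gap in medians against the 10-day gap in means. The first needs an assumed time distribution, or an exclusion rate that is not given, and it concerns only these outcomes. The second mixes scales. Nor does the article say that file access ends at release; it plans community follow-up and lists health records at follow-up.
- **These are secondary, descriptive outcomes.** The primary outcomes are feasibility rates and the trial is not powered for effectiveness. The Introduction also leaves open whether time to diagnosis is the right outcome for this population. This stands and limits the consequence.

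**Conclusion.** The point holds as a defect of outcome definition. The consultation outcome ends only at a confirmed ADHD diagnosis, the days outcome is ambiguous, and neither matches the decision in either direction that the article gives as the benefit of QbTest.

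If the generic mean or median were applied to those with a value, about 7 of 30 and 15 of 30 undecided participants would be left out, and the difference in mean days would fall from 25–39 to about 9–10.5. Those figures depend on community rates holding in custody, on the assumed Weibull shapes, and on a decided-only summary that the article implies but does not state. No size can be put on the loss through exclusions.

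The consequence is for the choice of endpoint and the planning values of the definitive trial. The documents do not support reading it as bias in an efficacy conclusion, because none is planned.

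**What to change.** Reword both outcomes to the same event: days, number of consultations and minutes from randomisation to a diagnostic decision, meaning ADHD confirmed or ADHD excluded.

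Report the numbers confirmed, excluded and undecided by arm, with all randomised as the denominator.

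Summarise time to decision with the undecided censored at their last file information, by Kaplan-Meier curve or restricted mean, in place of a mean or median among decided cases. The restricted mean is the safer summary: at the cited 50%, the control median falls at day 182 and might not be reached. Count consultations and minutes for everyone up to the decision or the last file information, and show the undecided separately because their counts are incomplete.

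The cost is a change of outcome wording and slightly more analysis. The same health files and clinician pro forma supply the data.

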For a formal clinical diagnosis of ADHD, a key aspect is the use of information from informants such as parents, teachers and health professionals.^6 7^ However, access to such information can be difficult to obtain and take a long time to receive, resulting in delays to receiving a confirmed diagnosis. The number of days young people spend in the CYPSE is relatively short.^22^ Therefore, informant information is very often not received before the young person leaves and returns back to the community. There is also evidence from a recent review within the CYPSE that establishments find it difficult to provide interventions to young people who are sentenced to fewer than 6 months, due to delays in assessment and/or diagnosis.^23^ All these factors can lead to delays in young people with ADHD receiving a diagnosis and accessing evidence-based treatment.

The impact of missed opportunities in diagnosis and accessing appropriate treatment can be significant. Young people with untreated ADHD in the CYPSE have been found to have an eightfold increased frequency of aggressive incidents in secure settings.^24 25^ Reducing violence and aggression is a key priority for Her Majesty’s Prison & Probation Service and Ministry of Justice, given the increasing rates within prisons.^26^ Treatment of adult offenders with ADHD using medication has demonstrated a reduction in reoffending of up to 41%.^27^ Therefore, there are also likely social and economic benefits to improving the diagnosis and access to treatment for young people with ADHD in the CYPSE.

QbTest (Qbtech) is a computer task that measures three core aspects of ADHD: attention, impulsivity and motor activity. Performance on the task provides information (via an immediate report) on the three symptom domains of ADHD and a ‘summary score’ based on deviation from a normative data set based on age group and gender. QbTest can be used with individuals with mild learning disabilities as instructions on how to complete the task are visual. Practitioners use the information from the QbTest report in conjunction with the clinical information (patient history, observation and ADHD symptom questionnaire) to inform their decision whether the young person has ADHD or not.

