#### Exclusion criteria

On remand (uncertain/sudden release).Non-English speaking (for pragmatic reasons, but will be included in the main trial testing applicability more widely).Previous or current confirmed diagnosis of ADHD.Currently receiving ADHD medication.Deemed to present risk to either the researcher or the staff.Unable to provide informed consent (over 16).Parental/legal guardian consent not received (under 16).

Potential participants will be identified by the prison healthcare team. The CHAT will identify potential participants displaying possible symptoms of ADHD, for example, any ADHD symptom codes in CHAT. Sentence status is accessible to healthcare staff via SystmOne (SystmOne is the clinical record system used within the CYPSE) and young people on remand will be excluded. Healthcare records will also be searched for previous or current confirmed diagnosis of ADHD and/or currently receiving ADHD medication and those young people will be excluded. The risk presented by potential participants will be assessed by the healthcare team, based on knowledge of the young person, information contained on SystmOne and discussion with prison staff and will take account of the likely risk in prison and community settings. Potential participants whose risk cannot be managed safely will be excluded.

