#### Follow-up (t2–t3)

If the young person is to be released during the study, the researcher will meet with them usually within the week prior to release. During this meeting, the researcher will confirm the contact information provided at baseline and make any amendments to the information (eg, change of phone number). Once discharged, the researcher will contact the participant again in the community, to maintain engagement, confirm contact details and arrange the follow-up in the community.

The 3-month follow-up can take place between 61 and 151 days post randomisation, although the researcher will endeavour to complete data collection as close to the 3-month (90-day) point. The 6-month follow-up can take place between 152 and 244 days postrandomisation, although the researcher will endeavour to complete data collection close to the 6-month point (182 days).

The follow-up may take place in prison or in the community, depending on if the young person has been discharged. In the community, the researcher will arrange to meet the young person at a convenient location. Where possible, interviews will be conducted in the premises of services that the young person is engaged with in order to minimise risk to the researcher. Where this is not possible, the researcher will arrange to conduct the interviews in a suitable location in the community and adhere to the Local Lone Working Policy.

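### Incidents and adjudications are defined as raw prison-file counts with no days-in-custody denominator, so the means, SDs and time trends carried to a definitive trial mix behaviour with length of stay

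*Protocol article*

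**What the plan says.** Under Secondary outcomes, the last item reads "Number of reordered behavioural incidents and adjudications are collecting using prison file information at baseline, 3 and 6 months". The unit is a number of events. No rate, days at risk, look-back period or rule for participants already released is attached to it.

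Data analysis and management applies one rule to everything: "All measures will be summarised by group across follow-up time with mean and SD for normally distributed data, median for skewed variables", with frequencies for categorical data.

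The article also says what happens to custody during the study. The Introduction states "The number of days young people spend in the CYPSE is relatively short". Follow-up (t2–t3) states "The follow-up may take place in prison or in the community, depending on if the young person has been discharged", and sets the timing: "The 3-month follow-up can take place between 61 and 151 days post randomisation" and "The 6-month follow-up can take place between 152 and 244 days postrandomisation", with target days of 90 and 182. The exclusion "On remand (uncertain/sudden release" removes young people whose release is least predictable. Sentenced participants who are released during follow-up stay in the trial.

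Two statements show what the outcome is for. The Introduction leaves open "if other outcomes, such as in aggressive incidents, are more important in this population", as against time to diagnosis. Sample size and recruitment says that the sample is meant to supply a mean and SD for each outcome measure.

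**The concern.** A prison file stops recording when the young person leaves. A low count can therefore mean few incidents or few days in custody, and a bare count cannot tell the two apart. The article's own account makes unequal custody time the expected case.

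The trial is descriptive, so no test is at risk. What is at stake is planning. This outcome is a candidate for greater weight in the definitive trial, and its mean and SD are among the things the feasibility sample should deliver. If those figures contain length of stay as well as behaviour, they are a poor guide to whether incidents are a usable outcome and to how large the next trial must be. A change from baseline to 3 and 6 months would be equally hard to read, because the period behind each count is not fixed.

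**Working it through.** **The plan's own figure.** The only design figure is the sample size: 30 + 30 = 60, which also equals 5 per month × 12 months. It reproduces and is not affected by this point.

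**Inputs from the article.** Visit windows of 61–151 and 152–244 days; target days 90 and 182; 30 per arm. The article gives no incident rate, no distribution of custody time and no between-person variation, so those below are assumptions.

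**Step 1: one participant.** Expected count = rate × days in custody. At a common rate, the count relative to someone held for 182 days is days/182, whatever the rate:

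- released at day 45: 45/182 = 0.25
- released at day 60: 60/182 = 0.33
- released at day 90: 90/182 = 0.49

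At an assumed 1 incident per 30 custody days, 90 days gives 3.0 and 182 days gives 6.1. At 0.5 per 30 days the pair is 1.5 and 3.0; at 2 per 30 days it is 6.0 and 12.1. Divided by custody days, the rate is the same in every case.

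**Step 2: visit windows, with no release at all.** If counting runs to the visit date, which the article does not say, exposure can vary by 151/61 = 2.5-fold at 3 months and 244/152 = 1.6-fold at 6 months. The gap between the two visits can be anything from 152 − 151 = 1 day to 244 − 61 = 183 days.

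**Step 3: mean and SD.** Assume Poisson counts at rate λ per day and custody time T uniform on 30 to 182 days. Then the mean of T is 106 days and its variance is 152²/12 = 1925. The count has mean λ × 106 and variance λ × 106 + λ² × 1925. The second term is length of stay alone.

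| Rate per 30 days | Mixed custody: mean, SD, CV | Fixed 182 days: mean, SD, CV | Variance due to custody time |
|---|---|---|---|
| 0.5 | 1.8, 1.5, 0.86 | 3.0, 1.7, 0.57 | 0.53/2.30 = 23% |
| 1 | 3.5, 2.4, 0.67 | 6.1, 2.5, 0.41 | 2.14/5.67 = 38% |
| 2 | 7.1, 4.0, 0.56 | 12.1, 3.5, 0.29 | 8.56/15.62 = 55% |

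These shares assume the same rate for everyone. With between-person variation in rates, custody time would account for a smaller share.

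**Step 4: chance imbalance between arms.** With the same custody distribution, SD(T) = √1925 = 43.9 days. The standard error of the arm difference in mean custody time is 43.9 × √(2/30) = 11.3 days, so the 95% range is about ±22 days around a mean of 106. At equal incident rates, arms at 117 and 95 days would show a ratio of mean counts of 95/117 = 0.81 and a rate ratio of 1.00.

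**Step 5: what a rate gains in the group comparison.** Simulation with 30 per arm, 0.03 incidents per day in both arms, and exponential custody time (mean 120 days before capping at 182) gives these 95% ranges for the ratio between arms:

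| Between-person variation (gamma dispersion) | Counts | Rates |
|---|---|---|
| none | 0.63–1.60 | 0.74–1.35 |
| 1 | 0.46–2.18 | 0.50–1.99 |
| 2 | 0.37–2.76 | 0.39–2.56 |

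The gain is clear if everyone has the same rate. It shrinks to little once people differ widely.

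**The case against.** The strongest reply is that denominators, look-back periods and offsets are analysis detail, which an article leaves to a full protocol or SAP. Neither is shown, and either could define a rate. This stands in part: the article does not rule out a rate, and nothing here shows that the final analysis will use counts. But the article does state the outcome unit, and that unit is a number summarised by group and time. The point is about that choice, in a setting where the article itself expects custody time to differ.

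A reader might infer that early release would make one arm look better behaved, so that the group contrast is biased. The documents do not support that. Allocation is individual, concealed and 1:1, so custody time is equal between arms in expectation unless the intervention changes release, and the article gives no mechanism for that. Chance imbalance adds variance, not bias. A ratio such as 0.81 in step 4 describes one extreme draw under an assumed custody distribution and predicts nothing about this trial.

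A reader might also infer that the baseline count covers only a few weeks, or that file counts stop on the visit date. The article states neither. It says that the health screen takes place in the first 10 days of admission, but not how long after admission baseline falls. The windows are set for follow-up data collection as a whole. Nor does it say how released participants are counted.

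Finally, this is a secondary outcome in a trial not powered for effectiveness, and all the primary outcomes concern feasibility. That limits the consequence, but it does not remove the use of the mean and SD for planning.

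**Conclusion.** The point holds as one about the unit of measurement. Followed as written, the plan yields counts that depend on days in custody as well as on behaviour. For one participant the dependence is proportional: about a quarter of the 182-day count if released at day 45, at any common rate. If counts run to the visit date, the windows add up to a 2.5-fold range of exposure at 3 months and 1.6-fold at 6 months. With no stated baseline period, baseline and follow-up counts may not be comparable.

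The main harm is to the mean, SD and time trend carried forward, and it needs no difference between arms. The effect on the group comparison is added noise. That noise could be material or slight, depending on the incident rate, the custody distribution and between-person variation, none of which the article gives. The change should be made, but the validity of the trial does not turn on it.

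**What to change.** - Record days in custody for each participant, using the release date from the prison file already being consulted.
- Report incidents and adjudications per 100 custody days, by arm, as total events over total custody days. If a model is fitted, use log custody days as the offset.
- Count over fixed intervals from randomisation (to day 90, and day 91 to 182), whatever the visit date. A participant released before an interval begins contributes no custody days to it and should not be entered as a zero count.
- State the baseline counting period and express baseline as a rate over it.
- Report custody days by arm alongside the rates, so that any imbalance is visible.

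The cost is one extra data field and a change of wording. Individual rates for participants released early will be imprecise, which is a reason to pool events and days within arm. The sample size does not change.
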